#### Relevant covariates

Covariates known to influence the selected biomarkers will be collected and included as covariates in the statistical analyses which include patient age, biological sex, and race [77]. The location of significant differences will be determined using post hoc tests with a Bonferroni correction.

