**Methods:**

We will enroll 30 individuals undergoing primary ACL reconstruction to participate in this IRB-approved multicenter clinical trial. This trial will target those at greatest risk of a more rapid PTOA onset (age range 25–50 with concomitant meniscus injury). Patients will be randomly assigned to a group instructed to take 10 mg of montelukast daily for 6 months following ACL reconstruction or placebo. Patients will be assessed prior to surgery and 1, 6, and 12 months following surgery. To determine if montelukast alters systemic inflammation following surgery, we will compare systemic concentrations of prostaglandin E2, monocyte chemoattractant protein-1, and pro-inflammatory cytokines between groups. We will also compare degradative changes on magnetic resonance imaging (MRI) collected 1 and 12 months following surgery between groups with reductions in early biomarkers of cartilage degradation assessed with urinary biomarkers of type II collagen breakdown and bony remodeling.

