**Discussion:**

There is a complex interplay between the pro-inflammatory intra-articular environment, underlying bone remodeling, and progressive cartilage degradation. PTOA affects multiple tissues and appears to be more similar to rheumatoid arthritis than osteoarthritis with respect to inflammation. There is currently no treatment to delay or prevent PTOA after ACL injury. Since there is a larger and more persistent inflammatory response after ACL reconstruction than the initial insult of injury, treatment may need to be initiated after surgery, sustained over a period of time, and target multiple mechanisms in order to successfully alter the disease process. This study will assess whether a 6-month postoperative course of oral montelukast affects multiple PTOA mechanisms. Because montelukast administration can be safely sustained for long durations and offers a low-cost treatment option, should it be proven effective in the current trial, these results can be immediately incorporated into clinical practice.

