Images collected at the University of Kentucky will then be transferred digitally to the University of California, San Francisco (UCSF) to be analyzed in the [name] Lab which is part of the Musculoskeletal and Quantitative Imaging Research Group (MQIR) at UCSF. Based on the high-resolution DESS images, articular cartilage will be segmented using a spline-based, semiautomatic technique. The T1ρ map will be created on a voxel-by-voxel basis using established fitting routines. The segmented masks will then be overlaid on the T1ρ maps after registration between DESS and T1ρ images, and mean T1ρ values will be calculated for the entire tibiofemoral cartilage, medial and lateral tibial plateau, medial and lateral femoral condyles, and the patellofemoral compartment will be calculated. Semiquantitative analyses will also be performed to assess abnormalities of the cartilage, meniscus, and bone marrow by an experienced musculoskeletal radiologist using the MRI Osteoarthritis Knee Score (MOAKS) [57].

In addition to assessing cartilage changes on MRI, we will also assess bone shape changes after ACL reconstruction. The bone area of the medial femoral condyle has been shown to increase within the first few months after ACL reconstruction [58, 59]. This is clinically meaningful as similar bony changes have been previously associated with progressive OA and within 6 months of ACL reconstruction correlated with subsequent patient-reported outcomes and MRI markers of cartilage quality at 3 years [58, 59]. [name] group at the Cleveland Clinic has previously established the methods to assess bone shape changes after ACL reconstruction [59]; images from both enrollment sites will be transferred digitally to the Cleveland Clinic for analysis.

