#### Secondary aim analysis

Variables will be assessed for normality and if normally distributed, baseline and 1-year T1ρ and T2 relaxation times as well as bone shape changes will be compared between groups using a 2 × 2 repeated measures ANOVA (group × time). Based on previous work, it is expected that the biomarkers of type II cartilage breakdown (CTXII) and bony remodeling (CTXIα) will not be normally distributed and it is anticipated that biomarker concentrations will be transformed using Box-Cox transformation [66]. A 2 × 4 repeated measures ANOVA (group × time) will be used to assess changes in biomarker concentrations between the montelukast and placebo groups. The ordinal semiquantitative MOAKS data will be compared between groups using chi-square or Fisher exact tests as appropriate.

For both primary and secondary analyses, in the case of participants that violate group allocation, we will perform Intention-to-Treat and Per Protocol analyses. We will not employ imputation methods in the case of missing data. No interim or other subgroup analyses will be performed.

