#### Power analysis

The primary outcome variable is the change in medial femoral condyle T1ρ relaxation time on MRI between 1 and 12 months postoperatively. Based on a previous study of ACL-reconstructed patients, we assume a standard deviation of 2.86 ms [78]. With a sample size of 15 patients per group, the trial is 81.5% powered to detect differences of 3.09 ms between groups (effect size = 1.08). A difference of this magnitude is feasible when one considers the differences previously noted for ACL reconstructed knees with concomitant meniscus tears [78]. This sample size is feasible for this multicenter trial. In a review of all ACL-injured patients seen at the University of Kentucky in 2019 ([name], unpublished raw data), 50 patients that met the study inclusion and exclusion criteria were seen. We anticipate a similar volume at the University of California San Francisco thereby providing a recruitment pool of approximately 100 eligible patients per year.

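### Three tests compete for primary status (PGE2, MCP-1 and medial femoral condyle T1ρ), and the only multiplicity rule, a Bonferroni correction of post hoc tests, does not control error across them

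*Protocol article*

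**What the plan says.** All references are to the protocol article.

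- **Power analysis.** One primary outcome variable is named: change in medial femoral condyle T1ρ between 1 and 12 months. On the size of the trial it says "the trial is 81.5% powered to detect differences of 3.09 ms between groups (effect size = 1.08"), with an SD of 2.86 ms and 15 patients per group. No significance level is given.
- **Aims and Primary aim analysis.** The primary aim is biochemical. Its hypothesis covers PGE2, MCP-1 and pro-inflammatory cytokines, and its analysis section specifies group-by-time ANOVAs for PGE2 and MCP-1. The abstract repeats the wider set: "we will compare systemic concentrations of prostaglandin E2, monocyte chemoattractant protein-1, and pro-inflammatory cytokines between groups".
- **Secondary aim analysis.** T1ρ appears here, without a region: "baseline and 1-year T1ρ and T2 relaxation times as well as bone shape changes will be compared between groups". CTXII, CTXIα and MOAKS follow.
- **MRI analyses.** "mean T1ρ values will be calculated for the entire tibiofemoral cartilage, medial and lateral tibial plateau, medial and lateral femoral condyles", and also for the patellofemoral compartment. That makes six T1ρ values per knee and visit.
- **Relevant covariates.** The single multiplicity provision: "The location of significant differences will be determined using post hoc tests with a Bonferroni correction".
- **Abstract, Discussion.** "should it be proven effective in the current trial, these results can be immediately incorporated into clinical practice". The article does not say which result would count as proof.

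**The concern.** A Bonferroni correction that locates differences after a significant ANOVA protects the comparisons among group-by-time cells of one variable. It does not limit how many variables can each yield a significant result at the full level. That would matter little if the article pointed to one decisive test. It points to two places instead: the power calculation identifies an imaging outcome, and the aims and analysis sections identify two serum markers. A positive result on any of the three could be presented as the primary result, each with support in the text.

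At stake is the meaning of a positive trial. With an inert drug, the chance of at least one apparently primary success is two to almost three times the nominal 5% if the tests are weakly correlated. The abstract links effectiveness to clinical practice without tying it to an endpoint. The unnamed T1ρ region adds a further choice, because any of six values could fill the place of the T1ρ comparison.

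**Working it through.** **1. Which alpha does the power figure imply?** Inputs from the Power analysis: difference 3.09 ms, SD 2.86 ms, n = 15 per group.

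- Effect size: d = 3.09 / 2.86 = 1.080, matching the stated 1.08.
- Two-sample t test: df = 2 × 15 − 2 = 28; noncentrality = d × √(n/2) = 1.080 × √7.5 = 2.96.
- Power = P(|T| > t-critical), with T noncentral t.

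| Level | Power |
|---|---|
| two-sided 0.05 | 0.815 |
| one-sided 0.05 | 0.893 |
| two-sided 0.025 | 0.720 |
| two-sided 0.05/3 = 0.0167 | 0.660 |

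Of these, only two-sided 0.05 reproduces 81.5%. The power calculation therefore spends the whole 0.05 on one T1ρ test. The level is an inference, since the article states none.

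**2. Which tests have a claim to be primary?** Medial femoral condyle T1ρ (Power analysis), PGE2 and MCP-1 (Primary aim analysis). That is three. The cytokines are in the primary hypothesis but not in the primary analysis, so they are not counted here.

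**3. Family-wise error for k tests at two-sided 0.05 each.** If independent, it is 1 − 0.95^k:

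- k = 2: 1 − 0.9025 = 0.0975
- k = 3: 1 − 0.8574 = 0.1426
- k = 8: 1 − 0.6634 = 0.3366

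If correlated, the test statistics are taken as normal with a common correlation ρ. The article gives no correlations, so the range is shown.

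| Set | k | ρ = 0 | ρ = 0.5 | ρ = 0.8 |
|---|---|---|---|---|
| PGE2, MCP-1 | 2 | 0.10 | 0.09 | 0.08 |
| plus condyle T1ρ | 3 | 0.14 | 0.13 | 0.10 |
| the variables named in the two analysis sections | 8 | 0.34 | 0.25 | 0.16 |

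The eight are PGE2, MCP-1, T1ρ, T2, bone shape, CTXII, CTXIα and MOAKS, counted once each.

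**4. Effect of the unnamed region.** If all six T1ρ values were tested at 0.05, that set alone would carry 0.14 (ρ = 0.8) to 0.26 (ρ = 0). The upper end is unrealistic, because the whole-tibiofemoral value contains four of the others. The article says the six are calculated; it does not say that each is tested.

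**The case against.** The strongest reply has four parts.

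*The article does name one primary outcome, with region and interval, and powers it.* This stands against the tempting stronger reading, that any significant marker or region could be offered as proof. The documents do not support that reading: no sentence says a single secondary marker would establish effectiveness. The abstract's sentence is conditional, and the closing Discussion softens it, speaking of informing larger trials and only potentially of practice. The reply does not remove the narrower point, because the aims and analysis sections give primary standing to other variables.

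*Handling of secondary outcomes commonly sits in an analysis plan, which is not shown.* This also stands. The lack of a rule for genuinely secondary outcomes is not the finding, and such outcomes need not all be adjusted. Which test is primary is a different matter: the article addresses it itself, in two incompatible ways.

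*The number of tests is not fixed.* Correct. A reader might count 15 (six T1ρ regions and three MOAKS tissues) or 28 (with T2 by region and cytokines added) and quote rates of 0.20 to 0.76. Those counts rest on splits that the article does not make, so no weight is placed on them. The result for three tests does not depend on them.

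*Alpha and correlation are assumed.* True. The power figure supports the level; the correlation has no source, hence the range.

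**Conclusion.** The point holds in a limited form. The article gives primary status to an imaging outcome in one place and to two serum markers in another, and its one multiplicity rule acts within a variable. Assuming two-sided 0.05 per test and correlations from 0.8 down to 0, the family-wise error is about 0.08 to 0.10 for PGE2 and MCP-1, and about 0.10 to 0.14 for the three rival primaries, against a nominal 0.05. For the eight named variables, about 0.16 to 0.34 describes how often a chance finding would appear somewhere among them. It is not the error rate of the efficacy claim. The post hoc Bonferroni sentence is not itself wrong, and the power arithmetic is sound for a single test at the full level. The change should be made before results are seen; it does not call the design into question.

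**What to change.** 1. Declare one primary outcome, state that it is tested at two-sided 0.05, and make the Aims, Primary aim analysis and Power analysis agree on it.
2. Alternatively, if PGE2 and MCP-1, or all three, are kept as joint primaries, use Holm across them and restate the power. At the planned standardised effect (1.08, or 3.09 ms for T1ρ), power at the first Holm step is about 72% with two tests and 66% with three. For three, 21 per group instead of 15 would restore 81.5% at that step. The article gives no planning effect for PGE2 or MCP-1, so 1.08 serves only as a yardstick for them.
3. In the Secondary aim analysis, name the medial femoral condyle as the T1ρ region tested, as the Power analysis already does.
4. Report the other T1ρ regions, T2, bone shape, CTXII, CTXIα, MOAKS and the cytokines as secondary or exploratory estimates with 95% confidence intervals.
5. Word the abstract's statement on effectiveness so that only the controlled primary test can support it. Keep the post hoc Bonferroni rule for its present purpose.

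With a single primary outcome the cost is wording only: no extra patients or data, and power for T1ρ stays at 81.5% if T1ρ is the one chosen. The price is that a nominally significant secondary marker or region can no longer be claimed as proof of efficacy.

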#### Power analysis

The primary outcome variable is the change in medial femoral condyle T1ρ relaxation time on MRI between 1 and 12 months postoperatively. Based on a previous study of ACL-reconstructed patients, we assume a standard deviation of 2.86 ms [78]. With a sample size of 15 patients per group, the trial is 81.5% powered to detect differences of 3.09 ms between groups (effect size = 1.08). A difference of this magnitude is feasible when one considers the differences previously noted for ACL reconstructed knees with concomitant meniscus tears [78]. This sample size is feasible for this multicenter trial. In a review of all ACL-injured patients seen at the University of Kentucky in 2019 ([name], unpublished raw data), 50 patients that met the study inclusion and exclusion criteria were seen. We anticipate a similar volume at the University of California San Francisco thereby providing a recruitment pool of approximately 100 eligible patients per year.

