## Methods/design

### Aims

The primary aim of this trial is to determine if a 6-month course of daily oral montelukast alters the biochemical mechanisms of PTOA when compared to placebo. The secondary aim is to assess the effect of oral montelukast on cartilage degradation and bone remodeling after ACL reconstruction. The hypotheses for the primary and secondary aims are that the use of montelukast after ACL reconstruction will:
Reduce peripheral concentrations of prostaglandin E2 (PGE2), monocyte chemoattractant protein-1 (MCP-1), and pro-inflammatory cytokines.Reduce degradative changes on magnetic resonance imaging (MRI) at 1 year, in association with reductions in early biomarkers of cartilage degradation (C-terminal crosslinked telopeptide type II collagen (CTXII)) and bony remodeling (an alpha isomerized version of the C-terminal crosslinked telopeptide of type I collagen (CTXIα)).

The complimentary aims will allow assessment of the joint as an organ and provide evidence for a novel, disease-modifying treatment approach with an approved, readily available, and widely used therapeutic agent to target multiple mechanisms of PTOA.

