#### Minimizing attrition

In order to maximize retention participants will be asked to provide alternate contacts and to specify whether study staff may leave messages or send mail. To promote attendance, patients will be contacted by phone both 1 week and 1 day prior to their study visits. In addition to ease the burden of attending subject visits they will be compensated for attending the follow-up study visits. The research coordinator and the PIs will track all study visits and will follow-up on any missed visits. Proactive strategies will be developed to work with participants who have trouble attending study visits. Participants will have 7:30 am–5 pm access to research personnel. In addition, while there are several study visits, all study visits can be scheduled to coincide with their physician follow-up appointments. We are currently employing these strategies in several ongoing trials and we have consistently resulted in less than 10% of ACL-reconstructed patients being lost to follow-up from our previous and ongoing clinical trials.

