### Statistical analysis

#### Primary aim analysis

Inflammatory biomarkers PGE2 and MCP-1 concentrations will be assessed for normality [12, 66]. If not normally distributed, biomarker concentrations will be transformed using Box-Cox transformation [66]. A 2 × 4 repeated measures ANOVA (group × time) will be used to assess changes in biomarker concentrations between the montelukast and placebo groups.

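### The power section names medial femoral condyle T1ρ change as the primary outcome, but the aims and analysis sections treat PGE2 and MCP-1 as primary and T1ρ as secondary

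*Protocol article*

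**What the plan says.** Four sections of the protocol article bear on what is primary.

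- **Aims:** "The primary aim of this trial is to determine if a 6-month course of daily oral montelukast alters the biochemical mechanisms of PTOA". The first hypothesis names PGE2, MCP-1 and pro-inflammatory cytokines. Imaging falls under the other aim: "The secondary aim is to assess the effect of oral montelukast on cartilage degradation and bone remodeling after ACL reconstruction".
- **Primary aim analysis:** "Inflammatory biomarkers PGE2 and MCP-1 concentrations will be assessed for normality", followed by a 2 × 4 (group × time) repeated measures ANOVA. T1ρ does not appear.
- **Secondary aim analysis:** T1ρ and T2 "relaxation times as well as bone shape changes will be compared between groups" in a 2 × 2 repeated measures ANOVA. No region is named, although the MRI analyses section derives T1ρ for the whole tibiofemoral cartilage, both tibial plateaus, both femoral condyles and the patellofemoral compartment.
- **Power analysis:** "The primary outcome variable is the change in medial femoral condyle" T1ρ, measured from month 1 to month 12 after surgery. Then: "With a sample size of 15 patients per group, the trial is 81.5% powered to detect differences of 3.09 ms between groups".

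Three further statements affect how far the power figure can be relied on. The Randomization section replaces participants who discontinue before the 6-month visit. The Secondary aim analysis section rules out imputation. The Minimizing attrition section reports "less than 10% of ACL-reconstructed patients being lost to follow-up" in the investigators' earlier and ongoing trials.

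**The concern.** A primary outcome should answer the primary aim and be tested in the primary analysis. Here the variable that carries the label is tested under the secondary aim, and the variables tested under the primary aim do not carry it. After unblinding, either T1ρ or the inflammatory markers could be presented as the main result, with text in the article to support each choice. With 30 participants and many biomarkers and imaging measures, that freedom matters.

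The sample-size justification is affected too. If T1ρ is primary, the trial has a stated basis for its size. If PGE2 and MCP-1 are primary, the article gives none.

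**Working it through.** **1. The designations side by side**

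| Section | Inflammatory markers | T1ρ |
|---|---|---|
| Aims | Primary aim | Secondary aim (within the MRI hypothesis) |
| Primary aim analysis | PGE2 and MCP-1 tested | Absent |
| Secondary aim analysis | Absent | Tested, no region named |
| Power analysis | Absent | Primary outcome, medial femoral condyle |

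No section ranks these variables or reconciles the two labels.

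**2. Reproducing the stated power**

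Inputs from the Power analysis section: difference 3.09 ms, SD 2.86 ms, 15 per group. Neither alpha nor sidedness is stated; two-sided 0.05 is assumed.

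- Effect size d = 3.09 / 2.86 = 1.080, matching the stated 1.08.
- Noncentrality = d × √(n₁n₂ / (n₁ + n₂)) = 1.0804 × √(225/30) = 2.96, on 28 degrees of freedom.
- Power of the two-sample t-test = 81.49%, matching 81.5%.

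One-sided 0.025 also gives 81.49%. One-sided 0.05 gives 89.3%, and the normal approximation at two-sided 0.05 gives 84.1%; neither of these matches. A t-test on change is equivalent to the group × time term of a 2 × 2 repeated measures ANOVA without covariates. The calculation therefore corresponds to the T1ρ analysis that sits under the secondary heading.

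**3. Power for PGE2 and MCP-1**

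This cannot be computed, because no SD or target difference is given. Purely to show how much depends on the unknown effect, a simple t-test at two-sided 0.05 with 15 per arm has these powers:

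| Assumed d | Power |
|---|---|
| 0.5 | 26% |
| 0.8 | 56% |
| 1.08 | 81.5% |

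**4. Error rate if the ambiguity were exploited (illustration only)**

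If success on any one of three independent endpoints, each tested at 0.05, counted as a positive trial, the family-wise error would be 1 − 0.95³ = 14.3%. Positive correlation between endpoints would lower it.

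**5. Sensitivity of 81.5% to losses after month 6**

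The endpoint needs a 12-month scan, replacement stops at the 6-month visit, and missing values are not imputed. Same d and alpha as in step 2:

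| Scans lost after month 6 | Per-arm split | Power |
|---|---|---|
| 0 | 15/15 | 81.5% |
| 1 | 15/14 | 80.0% |
| 2 | 14/14 or 15/13 | 78.6% or 78.4% |
| 3 | 14/13 or 15/12 | 76.9% or 76.5% |

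Three losses is an upper bound: 10% of 30 is 3, and this row places all of that loss after month 6.

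**The case against.** The strongest reply is that an aim and an outcome are different things. Only T1ρ is called the primary outcome variable; PGE2 and MCP-1 sit under a primary aim heading and are nowhere called primary outcomes or endpoints. On that reading there is one designated primary outcome, and its power calculation is correct. This stands in part: a reader might infer three competing primary outcomes, and the text does not go that far. It does not remove the conflict, because the one named primary outcome is analysed under the aim called secondary.

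A reader might also infer that PGE2, MCP-1 and T1ρ will each be tested at an unadjusted 5% and that any significant result will count as success. The article states no alpha and no success rule. The only correction it mentions is Bonferroni for post hoc tests, and an alpha rule across endpoints may sit in an analysis plan that is not shown. The 14.3% is therefore an illustration and not the trial's error rate. For the same reason no loss of T1ρ power from splitting alpha should be claimed: nothing in the article plans a split, and with T1ρ as sole primary none is needed.

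On attrition, it is fair to answer that the loss of under 10% covers whole trials and that early dropouts are replaced, with a randomization schedule prepared for 40. Most losses may therefore never reduce the 30. This makes the attrition point minor.

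The labelling conflict itself is not something an analysis plan would resolve, since such a plan would inherit both designations.

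**Conclusion.** The concern holds as a contradiction in the current text. The Power analysis section makes medial femoral condyle T1ρ change primary; the Aims and both analysis sections put the inflammatory biomarkers first and T1ρ second, with no region named for T1ρ. It must be fixed, because the article as written allows the main claim to rest on either.

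The 81.5% is arithmetically right under an assumed two-sided 0.05, but it says nothing about PGE2 or MCP-1. It also presumes that all 15 participants per arm have an evaluable 12-month scan. A few late losses would bring it to between about 80% and 76%, a modest effect secondary to the labelling conflict.

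**What to change.** Name one primary outcome and make the Aims, Primary aim analysis, Secondary aim analysis and Power analysis sections agree.

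- **Natural choice:** the 1-to-12-month change in medial femoral condyle T1ρ, since the trial is sized on it. Move it to the primary analysis, name the region there, state two-sided 0.05, and label PGE2 and MCP-1 secondary.
- **Alternative:** keep the biomarkers as primary. In that case, do not present 81.5% as power for the primary outcome; say which biomarker (or both, with an alpha rule) is primary, and supply an SD, a target difference and a power calculation for it.
- **Either way:** where the T1ρ power is quoted, add that it assumes 15 evaluable 12-month scans per arm and falls to about 80% with one loss after month 6, 78–79% with two and 76–77% with three.

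The first option costs only wording and a slightly less favourable power statement; no patients are added. The second requires a new calculation, and its effect on sample size cannot be judged from the figures given. Whether the registry entry needs a matching change cannot be judged from this article.
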